### Primary and secondary outcomes

Weekly alcohol consumption will be assessed by asking participants the number of standard drinks of alcohol they consumed last week (short-term recall method^26^). Frequency of heavy episodic drinking will be assessed by asking participants how many times they have consumed 4/5 (female/male) or more standard drinks of alcohol on one occasion the past month. These two outcomes are both part of the proposed core outcome set for brief alcohol interventions,^27–29^ and represent different risk behaviours which are sometimes found in the same individual and sometimes not. For instance, one may have a high weekly alcohol consumption, and thereby be at risk for negative health consequences, without consuming 4/5 or more drinks on the same occasion. Similarly, having one episode of heavy episodic drinking increases the risk of short-term consequences (such as injury) and long-term health consequences, but does not fulfil the criteria for total weekly consumption.

Diet and physical activity will be measured using a questionnaire based on the previously published questionnaire by the National Board of Health and Welfare in Sweden,^7^ and was further modified to also include portion sizes. The consumption of fruit and vegetables will be measured using two questions concerning the number of portions (100 g) of fruit and vegetables (respectively) the participants ate on average per day during the past week. Sugary drinks consumption will be measured by a question regarding the number of units (33 cl) of sugary drinks participants consumed the past week, and candy and snacks will be measured using a single question regarding number of servings consumed last week. MVPA will be estimated by summing responses to two questions regarding the number of minutes spent on moderate and vigorous physical activity, respectively, during the past week.

BMI will be measured by asking participants to report their weight and height.

Four-week point prevalence of smoking abstinence (no cigarettes the past 4 weeks) will be asked as a binary question. This is a suggested measure by the Society of Research on Nicotine and Tobacco.^30^ Participants who have smoked any cigarette the past 4 weeks will be asked for the number of cigarettes smoked the past week.

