## Analysis

All analyses will be done keeping all participants in the groups to which they were randomised. Analyses will be done using both available data and imputation. Imputation will be done using multiple imputation with chained equations.^36^ The implicit missing at random (MAR) assumption underlying this approach will be investigated by two attrition analyses: (1) if data are missing systematically then it may be the case that early responders (answering without reminders) differ from non-responders (requiring several attempts), and in extension that late responders are more alike non-responders. Therefore, one attrition analysis will regress primary outcomes against number of attempts to collect follow-up before a response was recorded; (2) we will further explore the MAR assumption by investigating if responders and non-responders are different with respect to baseline characteristics.

Groups will be contrasted using multilevel regression models with covariates for group by component interactions and participant level adaptive intercepts. Models of longitudinal data (primary outcomes and perceived stress) will include group by time by component interactions. We will explore pairwise interactions among components. Bayesian inference will be used to estimate the parameters of the models^37–39^ (see Sample Size for priors). For each coefficient of interest, we will report the marginal posterior probability of effect, and the median will be used as a point estimate of the magnitude of the effect. We will also report on 50% and 95% compatibility intervals.

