### Models

#### Primary and secondary outcomes

Analyses of primary outcomes will be conducted among those fulfilling the respective criteria for inclusion at baseline, for example, weekly alcohol consumption will be analysed among those who reported having consumed 10/15 (female/male) or more units of alcohol the past week. BMI, sugary drinks, candy/snacks, QoL and perceived stress will be analysed among all participants, and number of cigarettes smoked weekly among baseline smokers.

Weekly alcohol consumption, frequency of heavy episodic drinking per month, weekly intake of candy and snacks, number of sugary drinks per week and cigarettes smoked per week are all count variables that are likely skewed and over dispersed. Therefore, these outcomes will be analysed using negative binomial regression. If found not to be over dispersed, we will consider using normal regression (possibly log transformed). Average intake of fruit and vegetables per day, MVPA minutes per week, BMI, QoL and perceived stress will be analysed using normal regression (possibly log transformed). Point prevalence of smoking abstinence will be analysed using logistic regression.

All models will be adjusted for age, sex and mediators (importance, confidence and know-how) at baseline. Primary outcomes and perceived stress will be adjusted for their respective baseline values, except for smoking prevalence which will be adjusted by the weekly number of cigarettes smoked at baseline. BMI, sugary drinks and candy/snacks will be adjusted for baseline MVPA minutes per week and average intake of fruit and vegetables per day. Number of cigarettes smoked last week will be adjusted by its baseline value. QoL will be adjusted for perceived stress at baseline.

In addition to pairwise interactions between components, effect modification will be explored in all models to assess if any of the baseline characteristics moderate the effects of the components of the intervention.

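### BMI, sugary drinks, candy/snacks and QoL are modelled without their own baseline values, which costs precision on these secondary outcomes but causes no bias

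*Protocol article*

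**What the plan says.** The covariates are set out under Models, Primary and secondary outcomes.

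- Common to every model: "All models will be adjusted for age, sex and mediators (importance, confidence and know-how) at baseline".
- Own baseline included: "Primary outcomes and perceived stress will be adjusted for their respective baseline values", with smoking abstinence as the stated exception (it uses baseline weekly cigarettes). Also: "Number of cigarettes smoked last week will be adjusted by its baseline value".
- Own baseline not included: "BMI, sugary drinks and candy/snacks will be adjusted for baseline MVPA minutes per week and average intake of fruit and vegetables per day", and "QoL will be adjusted for perceived stress at baseline".

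The same section sets the analysis population: "BMI, sugary drinks, candy/snacks, QoL and perceived stress will be analysed among all participants". BMI and QoL are to be analysed by normal regression, drinks and snacks by negative binomial regression.

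Repeated measurement does not bring the starting value in by another route. The Analysis section says: "Models of longitudinal data (primary outcomes and perceived stress) will include group by time by component interactions". BMI, drinks, snacks and QoL are not in that list.

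On measurement, the Outcomes part of the article says "BMI will be measured by asking participants to report their weight and height" and gives no time points. The questionnaires are in supplemental Appendix A and the timeline is a figure; neither is shown.

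**The concern.** For an outcome that is stable within a person, the person's own starting value is usually by far the best predictor of the follow-up value. BMI over four months is such an outcome: adult height is fixed and weight moves little compared with the spread between people. Baseline activity and fruit and vegetable intake are likely to explain only a small part of that spread. The plan uses own-baseline adjustment for most other outcomes and gives no reason for treating these four differently. As written, a participant's starting level of BMI, drinks, snacks or QoL enters no model.

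What is at stake is the width of the intervals for six component effects on four secondary outcomes. If the baseline values exist, a large gain for BMI is being left unused at almost no cost.

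**Working it through.** **The plan's own figure.** The only precision-related figure is the simulated total of about 1,500 to 2,500 participants (Sample size). It concerns the primary outcomes, and its simulation inputs are not given, so it cannot be reproduced exactly. A simple two-group formula for d = 0.1 with two-sided 5% error gives totals of 1,538 at 50% power and 2,470 at 70% power, inside the stated range. This point does not affect that figure; it is used below only to choose an illustrative N.

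**Inputs.**
- From the article: each component is present for half the participants; BMI is analysed in everyone by normal regression; total N is about 1,500 to 2,500; the minimal effect for normal outcomes is 0.1 SD (stated for fruit/vegetables and physical activity).
- Assumed, because the article does not give them: the listed covariates explain R² = 0.05 of BMI variance; the baseline to follow-up correlation r; a BMI SD of 5; 2,000 analysed.

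**Step 1: residual variance.** With own baseline the unexplained fraction is taken as 1 − r²; with the listed covariates only it is 1 − R². The proportional cut is 1 − (1 − r²)/(1 − R²).

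| Assumed r | (1 − r²)/0.95 | Cut, R² = 0.05 | Cut, R² = 0.20 |
|---|---|---|---|
| 0.80 | 0.36/0.95 | 62% | 55% |
| 0.90 | 0.19/0.95 | 80% | 76% |
| 0.95 | 0.0975/0.95 | 90% | 88% |

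For less stable outcomes with R² = 0.05, r = 0.4 gives 1 − 0.84/0.95 = 12% and r = 0.7 gives 1 − 0.51/0.95 = 46%. That range is assumed for drinks, snacks and QoL. For drinks and snacks the formula is only a linear approximation, because their models are negative binomial.

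**Step 2: in BMI units.** For a 1:1 contrast, SE = 2 × SD × √(residual fraction)/√N. With SD 5 and N = 2,000:
- listed covariates only: 2 × 5 × √0.95/√2000 = 0.218, 95% half-width 0.43;
- own baseline, r = 0.90: 2 × 5 × √0.19/√2000 = 0.097, half-width 0.19;
- own baseline, r = 0.95: 2 × 5 × √0.0975/√2000 = 0.070, half-width 0.14.

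For scale, 1 kg at a height of 1.70 m is 1/1.70² = 0.35 units. That lies inside the first half-width and outside the other two. The N is generous: telephone follow-up collects primary outcomes only (Participant timeline and follow-ups), so BMI will probably have fewer responses.

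**Step 3: against the trial's own margin.** An SE of 0.218 is 0.218/5 = 0.044 SD. The 0.1 SD margin is 0.1/0.0436 = 2.3 SEs. At an estimate of zero and a near-flat prior, the probability that the effect lies within ±0.1 SD is about 98%, above the 95% that the futility criterion asks for. At N = 1,500 the SE is 0.0503 SD, the ratio 1.99 and the probability about 95%.

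**The case against.** The strongest reply is that these outcomes may not be asked at baseline. The covariate pattern fits that: the four outcomes without their own baseline receive related variables that are measured at entry, and the same four are missing from the longitudinal list. If so, the listed covariates are the only option for those already enrolled and nothing has been thrown away. This stands as a condition on the point, since the article does not settle it. The only hint the other way is in Interactions among health behaviours, where an exploratory analysis may refer to change in QoL, which would need a baseline QoL. The wording can also be read as applying change to perceived stress alone, and it says nothing about BMI, drinks or snacks.

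Three stronger readings are tempting, and the documents do not support them.
- A reader might infer that the plan discards 80% to 95% of the attainable information. That range needs r between about 0.90 and 0.976 with R² = 0.05, concerns BMI only, and presumes that baseline BMI is recorded.
- A reader might infer that the BMI result will be uninformative whatever the truth. Step 3 shows otherwise: at 2,000 analysed, the plan as written still meets the trial's own 0.1 SD yardstick, and nothing in the article says that the expected effects are smaller.
- A reader might infer bias or a threat to the main results. Components are randomised, so leaving out a prognostic covariate does not bias the contrasts. These outcomes are secondary, none is named in the Objectives, and the stopping criteria use the primary outcomes only.

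It is also fair to say that the methods and analysis plan were preregistered and that recruitment was already under way, so even a small model change has a procedural cost.

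**Conclusion.** The point holds as a matter of efficiency. The article specifies models for BMI, sugary drinks, candy/snacks and QoL that leave out each outcome's own baseline, unlike most other outcomes, and gives no reason. For BMI the avoidable residual variance is about 62% to 90% over r = 0.80 to 0.95 with R² = 0.05 (55% to 88% with R² = 0.20). For the other three it is roughly 12% to 46% under an assumed r of 0.4 to 0.7. None of these correlations comes from the documents, and the gain is available in full only if the baseline values are collected. It is a worthwhile improvement to secondary analyses, not a flaw in the trial's main inference.

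**What to change.** First, state in the article which of the four outcomes the baseline questionnaire records.

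- **Where the outcome is recorded at baseline:** add its own baseline value to the model, keep the covariates already listed, and record this as a change to the preregistered model. The only cost is documenting the change.
- **Where it is not:** the listed covariates remain the only option for those already enrolled. The short height, weight, sugary-drink and snack items can be added for remaining enrolees, with a missing-indicator for the others. This is acceptable because baseline answers, and whether they were asked for, precede randomisation and are independent of allocation. The cost is a small extra burden in a trial that tries to limit it, an amendment, and a gain that is only partial and shrinks as fewer enrolees remain (recruitment began in October 2021 and was expected to last no more than 12 months).

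Also reconcile Interactions among health behaviours with the QoL model. If change in QoL is to be analysed, baseline QoL must exist and should be in that model. If it does not exist, reword the exploratory analysis.

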#### Mediator outcomes

Mediators will be explored using a causal inference framework,^40–42^ using Bayesian inference to estimate the natural direct effect and natural indirect effect (as per the definitions of Pearl^42^). We will report on the posterior distributions of these two estimates, as well as the proportion of the total effect which is accounted for by the natural indirect effect. Four models will be created for each primary outcome measure, three which investigate the mediating factors on their own, and a fourth which incorporates all mediators at once. If any baseline characteristics were found to moderate the effects in the primary analysis, then additional mediator models will be created to include these as moderators.

#### Interactions among health behaviours

Outcome interactions, and determinants of such, will be investigated in an exploratory analysis. For instance, those who quit smoking may also be more likely to reduce their alcohol consumption, and this interaction may be moderated by baseline characteristics. In addition, we will investigate interactions between changes in perceived stress, QoL and behaviour change. Models to detect such interactions will be explored and findings will be used to create hypotheses for future research.

### Sample size

The trial will use a Bayesian group sequential design^18–20^ to monitor recruitment with interim analyses planned for every 50 participants completing the 4-month follow-up. Each of the primary outcomes will be modelled according to the analysis plan (see the Analysis section), and coefficients for dummy variables representing presence/absence of each component at each follow-up interval will be assessed for effect, harm and futility with respect to each outcome. We let ß_k, l, i_ represent the regression coefficient for component *k*, at time *I*, for outcome *i* and D all the data currently accumulated, then the target criteria will be:

Effect (fruit/veg. and physical activity): p(ß_k, l, i_ > 0 | D)>97.5% and p(ß_k, l, i_ > 0.10 | D)>50%.Harm (fruit/veg. and physical activity): p(ß_k, l, i_ < 0 | D)>97.5% and p(ß_k, l, i_ < -0.10 | D)>50%.Effect (alcohol and smoking): p(ß_k, l, i_ < 0 | D)>97.5% and p(ß_k, l, i_ < -0.10 | D)>50%.Harm (alcohol and smoking): p(ß_k, l, i_ > 0 | D)>97.5% and p(ß_k, l, i_ > 0.10 | D)>50%.Futility (all outcomes): p(−0.10 < ß_k, l, i_ < 0.10 | D)>95%.

Outcomes analysed using normal regression will be standardised when checking the above criteria. For the effect and harm criteria, we will use a standard normal prior for dummy covariates (mean=0, SD=1.0), and a slightly wider prior will be used for the futility criterion (mean=0, SD=2.0). The criteria should be viewed as targets, thus at each interim analysis we will evaluate each criterion and decide if we believe that recruitment should stop or continue. We will continue recruitment until one criterion is fulfilled for each component, for each outcome, at each follow-up interval. We will consider removing factors from the trial if the harm criteria are fulfilled for a component on all outcomes. We will not remove factors for which the effect or futility criteria are satisfied, as collecting additional data will facilitate reducing uncertainty regarding interaction effects. Note that we are estimating each component’s effect on each outcome, thus we are not a priori excluding any combination. If a component is ineffective with respect to a specific outcome, then this will be captured by the futility criteria, and will also be reported as a finding.

While the final sample size is not determined a priori, we conducted a series of simulations with effect sizes at the minimal value of the above criteria (0.1 Cohen’s d for fruit/veg and physical activity, 1.1 incidence rate ratios for alcohol and 1.1 ORs for smoking). Simulations suggested that approximately 1500–2500 participants will be necessary to recruit. However, the criteria will decide, not the simulations. Despite having more conditions than in a traditional two-arm trial (in this case 64 conditions), the factorial design is fully powered for each contrast.^17^ This can be understood by observing that half the study population are given access to each individual component (see online supplemental appendix table 1 in appendix B), thus the other half creates a contrast (a type of control).

Note that the Bayesian approach allows us to make unlimited looks at the data without worrying about multiplicities and error rates, as would be necessary using a frequentist approach.^43^ Also, since no fixed effect size is prespecified, we reduce the risk of stopping recruitment both too early and too late.^20^

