### Objectives

This study aims to estimate the effects of the components of a digital intervention on multiple health behaviours (alcohol, physical activity, diet and smoking) among individuals seeking help online. The objectives of the study are to:

Estimate the effects of a digital intervention’s different components on individual health behaviours:Weekly alcohol consumption and number of episodes per month of heavy drinking.Average daily fruit and vegetable consumption.Weekly moderate to vigorous physical activity (MVPA).Four-week point prevalence of smoking.Estimate the degree to which the effects of the components are mediated through perceived importance, confidence and know-how.Detect interactions among health behaviour change, for example, those who stop smoking may also reduce their alcohol consumption, and the degree to which this is moderated by the components of the intervention.

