##### Primary outcome measures

Alcohol: Weekly alcohol consumption; monthly frequency of heavy episodic drinking.Diet: Average daily consumption of fruit and vegetables.Physical activity: Weekly MVPA.Smoking: Four-week point prevalence of smoking abstinence.

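### The Effect and Harm criteria for smoking run in the wrong direction for the abstinence outcome the article models, unless smoking is coded as the event, which it does not state

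*Protocol article*

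**What the plan says.** Three places in the protocol article treat the smoking outcome as abstinence:

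- The outcome list (Primary outcome measures): "Smoking: Four-week point prevalence of smoking abstinence".
- The description of measurement (Outcomes, Primary and secondary outcomes): "Four-week point prevalence of smoking abstinence (no cigarettes the past 4 weeks) will be asked as a binary question".
- The model (Analysis, Models, Primary and secondary outcomes): "Point prevalence of smoking abstinence will be analysed using logistic regression".

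The Sample size section ties its decision criteria to those models: "Each of the primary outcomes will be modelled according to the analysis plan (see the Analysis section"). It also says what is tested: "coefficients for dummy variables representing presence/absence of each component at each follow-up interval will be assessed for effect, harm and futility".

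It then puts smoking on the same lines as alcohol: "Effect (alcohol and smoking): p(ß_k, l, i_ < 0 | D)>97.5" per cent, together with more than 50% probability that ß is below −0.10. Harm for alcohol and smoking is the same pair with the signs reversed. Fruit/vegetables and physical activity have the opposite direction, with Effect at ß above zero.

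Two places use the other wording. The Objectives name "Four-week point prevalence of smoking", and the covariate paragraph under Models refers in passing to smoking prevalence.

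The Harm label has one stated use: "We will consider removing factors from the trial if the harm criteria are fulfilled for a component on all outcomes".

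**The concern.** Alcohol consumption is better when lower; abstinence is better when higher. Putting both on one line with one sign can be right only if the smoking model is fitted with smoking, not abstinence, as the event. The article gives the model as one of abstinence and says nothing about recoding.

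At stake are the labels attached to each component for one of the four target behaviours, and the one stated rule for dropping a component on grounds of harm. If the rule is applied literally to the stated model, a component that increases quitting is classed as harmful for smoking and one that reduces quitting as effective.

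**Working it through.** **1. Link between threshold and effect size.** exp(0.10) = 1.105 and exp(−0.10) = 0.905, so the ±0.10 thresholds match the ratio of 1.1 used in the simulations. This does not reveal the coding. The same sentence gives an incidence rate ratio of 1.1 for alcohol, where Effect requires a ratio below 1, so these figures read as magnitudes without direction. The projected 1500–2500 participants cannot be reproduced because the simulation inputs are not given, and the point does not depend on it.

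**2. Sign of the coefficient.** Model as stated: logit P(abstinent) = … + ß × (component present). Then ß is the log odds ratio of abstinence, present versus absent, and benefit means ß > 0.

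| True effect on quitting | Sign of ß (abstinence as event) | Label as written | Label intended |
|---|---|---|---|
| Helps | positive | Harm | Effect |
| Hinders | negative | Effect | Harm |

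If smoking is the event, ß changes sign and the labels as written are correct.

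**3. How many coefficients.** There are 6 components, 2 follow-ups (2 and 4 months) and 5 primary outcomes: 6 × 2 × 5 = 60 coefficients, of which 6 × 2 = 12 concern smoking. Futility, −0.10 < ß < 0.10, is symmetric and does not depend on the coding.

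**4. Worked example (assumed counts).** 150/500 abstinent with the component, 100/500 without.

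- log OR = ln(150/350) − ln(100/400) = 0.539
- SE = √(1/150 + 1/350 + 1/100 + 1/400) = 0.148
- With the protocol's N(0, 1) prior, posterior variance = 1/(1/SE² + 1), giving mean 0.527 and SD 0.147
- P(ß>0) = 0.9998 and P(ß>0.10) = 0.998

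As written this meets Harm and not Effect. With the counts exchanged, so that the component hinders quitting, it meets Effect and not Harm. Under either correction below, both labels come out right.

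**5. How often a label would be attached, if abstinence is the event.** Normal-approximation posterior, N(0, 1) prior, 4000 replicates per setting, one look, one time point, no covariates. Abstinence without the component is assumed to be 20%, with the range over 10–30% in brackets. The number of analysed smokers is also assumed.

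| True OR of abstinence | Label as written | 300 smokers | 750 smokers | 1500 smokers |
|---|---|---|---|---|
| 2.0 | Harm | 72% (47–81) | 98% (89–99) | 100% (99.5–100) |
| 1.5 | Harm | 28% (16–36) | 63% (41–74) | 91% (71–96) |
| 0.667 | Effect | 22% (9–30) | 53% (31–66) | 83% (56–93) |

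For ORs of 2.0 and 1.5 the Effect label appears in at most 0.1% of replicates, and for 0.667 the Harm label rounds to 0.0%. At the protocol's own OR of 1.1, Harm is reached in only 2–19% of replicates over 300–2500 smokers and 10–30% abstinence. The rates depend on the assumptions; the reversal does not.

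**6. What follows for the decisions.**

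- *Stopping recruitment.* Recruitment continues until any one of Effect, Harm or futility is met for each coefficient. Effect and Harm are mirror images and the prior is centred at zero, so exchanging the two labels leaves the time at which this is met unchanged.
- *Removing a factor.* A component that worsens all behaviours has ß > 0 for both alcohol outcomes (Harm), ß < 0 for fruit/vegetables and activity (Harm), and ß < 0 for abstinence (Effect as written). Harm on all outcomes is then not met.
- *Final reporting.* The Analysis section reports posterior probabilities, medians and intervals. Recoding the event changes the sign of ß but not the evidence.

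**The case against.** The strongest reply is that the 0/1 coding of the logistic outcome is nowhere stated. A binary abstinence question can be fitted with either answer as the event, and the criteria are coherent if smoking is the event. The Objectives and the passing mention of smoking prevalence lean that way, and the preregistered analysis plan, not shown here, may state the coding. This stands to the extent that the interim code may already be correct. It does not remove the contradiction, because the article states both the model and the rule, and as stated they do not fit.

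The reply is also right about impact. The criteria are described as targets to be weighed at each interim analysis, and factor removal is only to be considered. A reader might infer that helpful components will in practice be declared harmful and dropped, or that the sample size is wrong. The documents support neither inference. Removal needs Harm on every outcome, so a reversed smoking label cannot by itself remove a component that benefits the other behaviours, and stopping does not depend on which of the two labels is met.

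**Conclusion.** The point holds as an error in the stated decision rule. For the model the article describes, the smoking Effect and Harm criteria are reversed, which affects 12 of 60 coefficients. This is conditional on abstinence being the modelled event, which the outcome list, the measurement and the model sentence all say and no section revokes.

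The operational consequence is narrow. It covers the smoking labels at interim analyses, and a removal rule that could not be met for a component harmful on everything. It would be too strong to say that all 12 coefficients will receive the wrong label: one that meets futility, or no criterion, is untouched. The percentages in the working rest on assumed abstinence rates, numbers of smokers and odds ratios, mostly well above the protocol's 1.1. They illustrate the reversal and do not forecast its cost.

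**What to change.** Choose one of two equivalent corrections:

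- Move smoking to the fruit/vegetable and physical activity lines: Effect if p(ß>0 | D) > 97.5% and p(ß>0.10 | D) > 50%, with Harm mirrored.
- Keep smoking with alcohol, and state that the modelled event is any smoking in the past four weeks.

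Then make the Objectives, the primary outcome list, the measurement description, the Models section and the Sample size criteria name the same event, and confirm that the interim code uses the same sign. If interim analyses have already been run, check the sign convention behind any smoking labels recorded. The cost is a short text change and a code check, with no additional participants or data.

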### Assignment of interventions

Randomisation will be fully automated and computerised. Block randomisation will be used to allocate participants to the 64 conditions (random block sizes of 64 and 128). Neither research personnel nor participants will be able to influence allocation.

Research personnel will be blind to allocation throughout the trial. All participants will have access to the intervention, although with different components, and they will not be made aware of the other available conditions and will therefore be blind to allocation.

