## Ethics and dissemination

The study was approved by the Swedish Ethical Review Authority on 2021-08-11 (Dnr 2021-02855). Participants are likely to have been motivated to sign up for the trial by the potential of receiving novel support, leading to a risk of opportunity cost if the intervention only exerts small effects on behaviour. However, considering that current prevention efforts seem to not be enough to reduce the prevalence of unhealthy behaviours, and the potential effects and reach a digital multiple health behaviour change intervention could have among those seeking help online, this risk was deemed acceptable.

Recruitment began in October 2021, and we anticipate that recruitment will last no more than 12 months. A final dataset will therefore be available in January 2023, and findings will be subsequently submitted for peer-review in open access journals.

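### The sample-size section gives two incompatible stopping rules and no limit, and the mandatory rule is very unlikely to end within 1,500–2,500 participants

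*Protocol article*

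**What the plan says.** All of the stopping text is in the Sample size section of the protocol article.

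- **Looks:** "interim analyses planned for every 50 participants completing the 4-month follow-up". At each look, every component's coefficient for every primary outcome and follow-up is checked against effect, harm and futility criteria. Futility requires more than 95% posterior probability that the coefficient lies between −0.10 and 0.10.
- **Discretionary rule:** "The criteria should be viewed as targets, thus at each interim analysis we will evaluate each criterion and decide if we believe" recruitment should stop or continue.
- **Mandatory rule, in the next sentence:** "We will continue recruitment until one criterion is fulfilled for each component, for each outcome, at each follow-up interval".
- **Size:** "While the final sample size is not determined a priori", simulations were run at the smallest effects of interest. "Simulations suggested that approximately 1500–2500 participants will be necessary to recruit", followed by "However, the criteria will decide, not the simulations".
- **Time:** Ethics and dissemination offers only an expectation: "we anticipate that recruitment will last no more than 12 months".

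Two other sections matter. Under Models, each primary outcome is analysed only in participants who met that outcome's own inclusion criterion at baseline. Under Assignment of interventions, "Research personnel will be blind to allocation throughout the trial".

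**The concern.** A criterion that is only a target cannot also be one that must be met before recruitment ends. If the mandatory rule could finish near the stated range, the conflict would be a matter of drafting. If it could not, judgement at an interim look would decide when the trial ends, and the article sets no boundary on that judgement. The simulated 1,500–2,500 would then describe neither the mandatory rule nor the discretionary one, because an expected sample size holds only for the rule that is followed. Readers of the results could not tell whether the final size came from the criteria or from a view of the emerging estimates.

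**Working it through.** **Inputs from the article.** Six components; five primary outcomes (weekly alcohol, heavy episodic drinking, fruit and vegetables, physical activity, smoking abstinence); outcomes at 2 and 4 months; half of participants on each component; the criteria and priors as stated. Cells to resolve: 6 × 5 × 2 = 60.

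**The plan's own figure.** The 1,500–2,500 cannot be strictly reproduced. The article does not give the outcome rates, dispersion, baseline correlation, share eligible per outcome or attrition that were simulated.

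**Futility bound.** The most favourable case is an estimate of exactly zero. It needs SE ≤ 0.10/1.96 = 0.05102. The futility prior (SD 2) adds precision of only 0.25 to about 384, so it is ignored.

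- Standardised outcome, SE = 2/√N: N = 4/0.05102² ≈ 1,537. With an assumed baseline correlation of 0.5, multiply by 1 − 0.25: about 1,152.
- Smoking log-odds ratio, SE = 2/√(N p(1−p)): at p = 0.5, the best case, N = 4/(0.05102² × 0.25) ≈ 6,147 baseline smokers. At an assumed 20% abstinence it is about 9,604.
- Alcohol counts depend on mean and dispersion, which are not given. Assuming means of 4 to 15 and negative binomial size of 1 to 5, about 410 to 1,921 eligible drinkers.

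**What this means for smoking.** Suppose all 2,500 recruits smoked and half abstained. Then SE = 2/√(2,500 × 0.25) = 0.08. At a zero estimate, the probability inside ±0.10 is 2Φ(0.10/0.08) − 1 = 0.79, short of 0.95. A smoking cell could close by 2,500 only through effect or harm, which needs an estimate at least 1.96 × 0.08 = 0.157 from zero. All twelve smoking cells (6 × 2) would have to show this. Real subsets are smaller and the hurdle is higher.

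**Simulation of the written rule.** The stated criteria and priors were applied with a look every 50 participants, up to 20,000. Assumptions: every cell a standardised outcome, no attrition, everyone eligible, no baseline adjustment, independent cells with the same true effect. There were 2,000, 400 and 100 replicates for 1, 12 and 60 cells. The text does not say whether all cells must be satisfied at the same look or each only once, so both were run. Entries are median stopping size (share stopped by 2,500).

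| Cells, true effect | All at the same look | Each met once |
|---|---|---|
| 1, none | 1,700 (86%) | 1,700 (86%) |
| 1, 0.10 | 850 (86%) | 900 (87%) |
| 12, none | 4,750 (0.5%) | 3,250 (20%) |
| 12, 0.10 | 97% not stopped by 20,000 (0.75%) | 5,300 (16%) |
| 60, none | 6,400 (0%) | 4,600 (1%) |
| 60, 0.10 | none stopped by 20,000 | 16,100 (0%) |

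The stated range is close to what one cell with no effect needs. It is far below what 60 cells need. A baseline correlation of 0.5 would scale the 60-cell, no-effect medians to about 0.75 × 6,400 = 4,800 and 0.75 × 4,600 = 3,450, still above 2,500. Treating smoking as a standardised outcome makes these figures optimistic. At a true effect of exactly 0.10, the posterior median falls on either side of 0.10 about equally often however large N becomes, so cells keep moving in and out of the effect criterion.

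**Looks during recruitment.** At 1,500/12 = 125 to 2,500/12 = 208 recruits per month, those with 4-month data by month 12 are 8 × 125 = 1,000 to 8 × 208 = about 1,667. That is 20 to 33 looks without attrition.

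**The case against.** Several points on the other side are sound.

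- An uncapped Bayesian sequential design is a declared and legitimate choice, and the article argues that posterior inference tolerates repeated looks. That does not reconcile the two sentences. It also does not rescue an expected sample size, which depends on the rule.
- The remark that the criteria will decide contrasts them with the simulated size, not with the team's judgement. It supports the mandatory reading only weakly; the contradiction rests on the two adjacent sentences.
- Twelve months may serve as a practical limit. It is worded as an expectation, so it does not bind.
- The simulated stopping sizes rest on independent cells and a common true effect. Positive correlation between cells would shorten them. The smoking bound uses neither assumption.
- Components with clear effects close sooner. The bound concerns cells with little or no effect, and with 60 cells some are likely.

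A reader might go further and infer that staff are unblinded at each look and then phone participants for self-reported outcomes, contrary to the blinding statement. The documents do not support that. The article does not say who runs the interim analyses, whether component labels are masked, or whether callers see results, and the preregistered plan, not shown here, may settle this. An aggregate component coefficient does not reveal which of 64 conditions a participant received. The limitations section discloses the risk from calls, judges exact deduction of allocation unlikely, and restricts what callers may ask.

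A reader might also count 1,500/50 = 30 to 2,500/50 = 50 looks as affecting the stopping decision. Looks count 4-month completers, so those after recruitment closes cannot affect it.

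**Conclusion.** The point holds. Two adjacent sentences state different stopping rules, and nothing in the article bounds recruitment if the criteria stay unmet. The conflict has practical weight because the mandatory rule would very probably run past 2,500. The firmest evidence is the smoking outcome, whose futility bound is about 2.5 times the top of the range (6,147/2,500) even if every recruit smoked. The simulation agrees, with 0–1% of 60-cell, no-effect trials stopped by 2,500, conditional on its assumptions. On this reading, discretion or an unstated limit would end recruitment. The analysis itself is not invalidated and no breach of blinding is shown. The stopping rule and its expected size should be corrected.

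**What to change.** 1. Replace the two sentences with one rule: recruitment stops when every cell meets a criterion, or at a fixed maximum sample size or calendar date, whichever comes first. Say whether cells must be satisfied at the same look or each only once.
2. State that cells unresolved at that point are reported as inconclusive.
3. Present 1,500–2,500 as the expected size only if it comes from the rule actually followed; otherwise re-simulate for all 60 cells, using each outcome's eligible subset.
4. As a secondary, inexpensive safeguard, have the interim script report criteria status under masked component codes. Include a flag for harm on all outcomes, so that the provision on removing factors still works. Withhold interim estimates from staff who phone participants.

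The cost is redrafting, a re-run of the simulations and a change to the interim output. The team gives up some discretion, and some cells may end as inconclusive.
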